### 12.1. Definition of Adverse Events

An AE is any untoward medical occurrence in a patient or clinical investigation subject, temporally associated with the use of a medicinal product, whether or not considered related to the medicinal product.

Note: An AE can therefore be any unfavorable and unintended sign (including an abnormal laboratory finding), symptom, or disease (new or exacerbated) temporally associated with the use of a medicinal product.

Events meeting the definition of an AE **include**:

- Any abnormal laboratory test results (hematology, clinical chemistry, or urinalysis) or other safety assessments (e.g., ECGs, radiological scans, vital signs measurements), including those that worsen from baseline, and felt to be clinically significant in the medical and scientific judgement of the investigator.

- Exacerbation of a chronic or intermittent pre-existing condition including either an increase in frequency and/or intensity of the condition.
- New conditions detected or diagnosed after investigational product administration even though it may have been present prior to the start of the study.
- Signs, symptoms, or the clinical sequelae of a suspected interaction.
- Signs, symptoms, or the clinical sequelae of a suspected overdose of either investigational product or a concomitant medication (overdose per se will not be reported as an AE/SAE).

Events that **do not** meet the definition of an AE include:

- Any clinically significant abnormal laboratory findings or other abnormal safety assessments that are associated with the underlying disease, unless judged by the investigator to be more severe than expected for the subject's condition.
- The disease/disorder being studied, or expected progression, signs, or symptoms of the disease/disorder being studied, unless more severe than expected for the subject's condition.
- Medical or surgical procedure (e.g., endoscopy, appendectomy); the condition that leads to the procedure is an AE.
- Situations where an untoward medical occurrence did not occur (social and/or convenience admission to a hospital).
- Anticipated day-to-day fluctuations of pre-existing disease(s) or condition(s) present or detected at the start of the study that do not worsen.

## 12.2. Definition of Serious Adverse Events

If an event is not an AE per Section 12.1, then it can not be an SAE even if serious conditions are met (e.g., hospitalization for signs/symptoms of the disease under study, death due to progression of disease, etc).

An SAE is any untoward medical occurrence that, at any dose:

- a. Results in death
- b. Is life-threatening

NOTE: The term 'life-threatening' in the definition of 'serious' refers to an event in which the subject was at risk of death at the time of the event. It does not refer to an event, which hypothetically might have caused death, if it were more severe.

- c. Requires hospitalization or prolongation of existing hospitalization

NOTE: In general, hospitalization signifies that the subject has been detained (usually involving at least an overnight stay) at the hospital or emergency ward for observation and/or treatment that would not have been appropriate in the physician's office or out-patient setting. Complications that occur during hospitalization are AEs. If a complication prolongs hospitalization or fulfills any other serious criteria,

the event is serious. When in doubt as to whether “hospitalization” occurred or was necessary, the AE should be considered serious.

Hospitalization for elective treatment of a pre-existing condition that did not worsen from baseline is not considered an AE.

d. Results in disability/incapacity, or

NOTE: The term disability means a substantial disruption of a person’s ability to conduct normal life functions. This definition is not intended to include experiences of relatively minor medical significance such as uncomplicated headache, nausea, vomiting, diarrhea, influenza, and accidental trauma (e.g. sprained ankle) which may interfere or prevent everyday life functions but do not constitute a substantial disruption.

e. Is a congenital anomaly/birth defect

f. Medical or scientific judgment should be exercised in deciding whether reporting is appropriate in other situations, such as important medical events that may not be immediately life-threatening or result in death or hospitalization but may jeopardize the subject or may require medical or surgical intervention to prevent one of the other outcomes listed in the above definition. These should also be considered serious. Examples of such events are invasive or malignant cancers, intensive treatment in an emergency room or at home for allergic bronchospasm, blood dyscrasias or convulsions that do not result in hospitalization, or development of drug dependency or drug abuse.

g. Is associated with liver injury **and** impaired liver function defined as:

- ALT  $\geq$  3xULN, and
- total bilirubin  $\geq$  2xULN or INR  $>$  1.5.

NOTES:

Bilirubin fractionation should be performed if testing is available. If fractionation is unavailable, urinary bilirubin is to be measured via dipstick (a measurement of direct bilirubin, which would suggest liver injury).

If INR is obtained, the value is to be recorded on the SAE form. INR elevations  $>$ 1.5 suggest severe liver injury.

### 12.3. Method of Detecting AEs and SAEs

Care will be taken not to introduce bias when detecting AEs and/or SAEs. Open-ended and non-leading verbal questioning of the subject is the preferred method to enquire about AE occurrence. Appropriate questions include:

- “How are you feeling?”
- “Have you had any medical problems since your last visit/contact?”
- “Have you taken any new medicines, other than those provided in this study, since your last visit/contact?”

## **12.4. Recording of AEs and SAEs**

When an AE/SAE occurs, it is the responsibility of the investigator to review all documentation (e.g., hospital progress notes, laboratory, and diagnostics reports) relative to the event. The investigator will then record all relevant information regarding an AE/SAE in the appropriate data collection tool.

It is not acceptable for the investigator to send photocopies of the subject's medical records to GSK in lieu of completion of the GSK, AE/SAE data collection tool. However, there may be instances when copies of medical records for certain cases are requested by GSK. In this instance, all subject identifiers, with the exception of the subject number, will be blinded on the copies of the medical records prior to submission of to GSK.

The investigator will attempt to establish a diagnosis of the event based on signs, symptoms, and/or other clinical information. In such cases, the diagnosis will be documented as the AE/SAE and not the individual signs/symptoms.

Subject-completed health outcomes questionnaires and the collection of AE data are independent components of the study. Responses to each question in the health outcomes questionnaire will be treated in accordance with standard scoring and statistical procedures detailed by the scale's developer. The use of a single question from a multidimensional health survey to designate a cause-effect relationship to an AE is inappropriate.

## **12.5. Evaluating AEs and SAEs**

### **12.5.1. Assessment of Intensity**

The investigator will make an assessment of intensity for each AE and SAE reported during the study and will assign it to one of the following categories:

Mild: An event that is easily tolerated by the subject, causing minimal discomfort and not interfering with everyday activities.

Moderate: An event that is sufficiently discomfoting to interfere with normal everyday activities.

Severe: An event that prevents normal everyday activities.

An AE that is assessed as severe will not be confused with an SAE. Severity is a category utilized for rating the intensity of an event; and both AEs and SAEs can be assessed as severe. An event is defined as 'serious' when it meets at least one of the pre-defined outcomes as described in the definition of an SAE.

### **12.5.2. Assessment of Causality**

The investigator is obligated to assess the relationship between investigational product and the occurrence of each AE/SAE. A "reasonable possibility" is meant to convey that

there are facts/evidence or arguments to suggest a causal relationship, rather than a relationship cannot be ruled out. The investigator will use clinical judgment to determine the relationship. Alternative causes, such as natural history of the underlying diseases, concomitant therapy, other risk factors, and the temporal relationship of the event to the investigational product will be considered and investigated. The investigator will also consult the Investigator Brochure (IB) and/or Product Information, for marketed products, in the determination of his/her assessment.

There may be situations when an SAE has occurred and the investigator has minimal information to include in the initial report to GSK. However, **it is very important that the investigator always make an assessment of causality for every event prior to the initial transmission of the SAE data to GSK.** The investigator may change his/her opinion of causality in light of follow-up information, amending the SAE data collection tool accordingly. The causality assessment is one of the criteria used when determining regulatory reporting requirements.

## **12.6. Follow-up of AEs and SAEs**

After the initial AE/SAE report, the investigator is required to proactively follow each subject at subsequent visits/contacts. All AEs and SAEs will be followed until resolution, until the condition stabilizes, until the event is otherwise explained, or until the subject is lost to follow-up.

The investigator is obligated to perform or arrange for the conduct of supplemental measurements and/or evaluations as may be indicated or as requested by GSK to elucidate as fully as possible the nature and/or causality of the AE or SAE. The investigator is obligated to assist. This may include additional laboratory tests or investigations, histopathological examinations or consultation with other health care professionals. If a subject dies during participation in the study or during a recognized follow-up period, the investigator will provide GSK with a copy of any post-mortem findings, including histopathology (may not be required for studies where death is an endpoint).

New or updated information will be recorded in the originally completed data collection tool. The investigator will submit any updated SAE data to GSK within the designated reporting time frames.

## **12.7. Prompt Reporting of SAEs to GSK**

Once the investigator determines that an event meets the protocol definition of an SAE, the SAE will be reported to GSK **within 24 hours**. Any follow-up information on a previously reported SAE will also be reported to GSK within 24 hours.

If the investigator does not have all information regarding an SAE, he/she will not wait to receive additional information before notifying GSK of the event and completing the appropriate data collection tool. The investigator will always provide an assessment of causality at the time of the initial report as described in Section [12.5.2](#), Assessment of Causality.

The primary mechanism for reporting SAEs to GSK will be the electronic data collection tool (e.g., InForm system). If the electronic system is unavailable for greater than 24 hours, the site will use the paper SAE data collection tool and fax it to the GSK Medical Monitor or protocol contact. Then the site will enter the serious adverse event data into the electronic system as soon as it becomes available.

After the study is completed at a given site, the electronic data collection tool (e.g., InForm system) will be taken off-line to prevent the entry of new data or changes to existing data. If a site receives a report of a new SAE from a study participant or receives updated data on a previously reported SAE after the electronic data collection tool has been taken off-line, the site can report this information on a paper SAE form or to their GSK protocol contact by telephone.

GSK contacts for SAE receipt can be found at the beginning of this protocol on the Sponsor/Medical Monitor Contact Information page.

## **12.8. Regulatory Reporting Requirements For SAEs**

Prompt notification of SAEs by the investigator to GSK is essential so that legal obligations and ethical responsibilities towards the safety of subjects are met.

GSK has a legal responsibility to notify both the local regulatory authority and other regulatory agencies about the safety of a product under clinical investigation. GSK will comply with country specific regulatory requirements relating to safety reporting to regulatory authorities, IRBs/IECs and investigators.

Investigator safety reports are prepared for suspected unexpected serious adverse reactions according to local regulatory requirements and GSK policy and are forwarded to investigators as necessary. An investigator who receives an investigator safety report describing an SAE(s) or other specific safety information (e.g., summary or listing of SAEs) from GSK will file it with the IB and will notify the IRB/IEC, if appropriate according to local requirements.

## **13. LIVER CHEMISTRY FOLLOW-UP PROCEDURES**

Refer to the diagram in [Appendix 1](#) for a visual presentation of the procedures listed below.

The procedures listed below are to be followed if a subject meets any of the liver chemistry stopping criteria defined in Section [4.5.5.1](#):

- Immediately and permanently withdraw the subject from investigational product
- Notify the GSK medical monitor within 24 hours of learning of the abnormality to confirm the subject's investigational product cessation and follow-up.
- Complete the "Safety Follow-Up Procedures" listed below.

- Complete the liver event case report forms. If the event also meets the criteria of an SAE (see Section 12.2), the SAE data collection tool will be completed separately with the relevant details.
- Upon completion of the safety follow-up permanently withdraw the subject from the study and do not rechallenge with investigational product.

**Safety Follow-Up Procedures for subjects with ALT  $\geq 3$ xULN and bilirubin  $\geq 2$ xULN (Stopping Criterion #1):**

- This event is considered an SAE (see Section 12.2). Serum bilirubin fractionation should be performed if testing is available. If fractionation is unavailable, urinary bilirubin is to be measured via dipstick (a measurement of direct bilirubin, which would suggest liver injury).
- Make every reasonable attempt to have the subjects return to the clinic (within 24 hours) for repeat liver chemistries, additional testing and to be monitored closely (with specialist or hepatology consultation recommended).
- Monitor subjects twice weekly until liver chemistries (ALT, AST, alkaline phosphatase, bilirubin) resolve, stabilize or return to within baseline values.

**Safety Follow-Up Procedures for subjects with ALT  $\geq 5$ xULN or ALT  $\geq 3$ xULN who have hepatitis symptoms or rash, can't be monitored for 4 weeks or have elevations that persist  $\geq 4$  weeks (Stopping Criteria #2 - #5):**

- Make every reasonable attempt to have the subject return to the clinic within 24-72 hrs for repeat liver chemistries and additional testing.
- Monitor subjects weekly until liver chemistries (ALT, AST, alkaline phosphatase, bilirubin) resolve, stabilize or return to within baseline values.

**Safety Follow-Up Procedures for subjects with ALT  $\geq 3$ xULN and  $< 5$ xULN and bilirubin  $< 2$ xULN, who do not exhibit hepatitis symptoms or rash:**

- Notify the GSK medical monitor within 24 hours of learning of the abnormality to discuss subject safety.
- Liver chemistries (ALT, AST, alkaline phosphatase, bilirubin) can be monitored weekly for up to 4 weeks.
- If at any point these subjects meet the liver chemistry stopping criteria (outlined in Section 4.5.5.1), perform additional testing and continue safety follow-up until liver chemistries resolve, stabilize or return to baseline values.
- After 4 weeks of monitoring, if ALT  $< 3$ xULN and bilirubin  $< 2$ xULN, subjects must be monitored twice monthly until liver chemistries normalize or return to within baseline values.

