#### 4.5.4. Liver Function Criteria

Liver chemistry threshold stopping criteria have been designed to assure subject safety. When subjects meet the following liver chemistry threshold criteria, the subject will be not entered in the second cohort and must be permanently withdrawn from the study, and the subject monitored until liver chemistries resolve, stabilize, or return to baseline values. The subject must be permanently withdrawn from the study if he/she meets following criteria:

- ALT  $\geq$  3xULN **and** bilirubin  $\geq$  1.5xULN (>35% direct).
- ALT  $\geq$  3xULN.

Subjects with ALT  $\geq$  3xULN **and** bilirubin  $\geq$  1.5xULN (>35% direct bilirubin; bilirubin fractionation required) must be required to return to the clinic (within 24 hours) for repeat liver chemistries and additional testing, and monitored closely (with specialist or hepatology consultation recommended). This event must be reported to GSK within 24 hours of learning of its occurrence. Subjects must be monitored twice weekly until liver chemistries (ALT, AST, alkaline phosphatase, bilirubin) resolve, stabilize or return to within baseline values.

Subjects with ALT  $\geq$  3xULN must be monitored weekly until liver chemistries (ALT, AST, alkaline phosphatase, bilirubin) resolve, stabilize or return to within baseline values. This event must be reported to GSK within 24 hours of learning of its occurrence.

In all the above situations, every attempt must be made to obtain the following:

- Viral hepatitis serology including:
  - Hepatitis A IgM antibody.
  - Hepatitis B surface antigen and Hepatitis B Core Antibody (IgM).
  - Hepatitis C RNA.
  - Cytomegalovirus IgM antibody.
  - Epstein-Barr viral capsid antigen IgM antibody (or if unavailable, obtain heterophile antibody or monospot testing).
  - Hepatitis E IgM antibody (if subject resides outside the USA or Canada, or has travelled outside USA or Canada in past 3 months).
- Blood sample for pharmacokinetic (PK) analysis, obtained within 56 days of last dose. Record the date/time of the PK blood sample draw and the date/time of the last dose of investigational product prior to blood sample draw on the CRF.

- Serum creatinine phosphokinase (CPK) and lactate dehydrogenase (LDH).
- Fractionate bilirubin, if bilirubin  $\geq 1.5 \times \text{ULN}$ .

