| Hema/Chem/Urinalysis tests                                                      | x                                                        | x                                    |                                                                          |     |     |     |     |     |     |     |     |      |                                  |      |      |      |      |      |      |      |      |      |      | x                       | x    |        |
| Anti-GSK933776 antibody Sampling                                                |                                                          | x                                    |                                                                          |     |     |     |     |     |     |     |     |      |                                  |      |      |      |      |      |      |      |      |      |      | x                       | x    |        |
| Urine Drug/Alcohol Screen                                                       | x                                                        | x                                    |                                                                          |     |     |     |     |     |     |     |     |      |                                  |      |      |      |      |      |      |      |      |      |      |                         |      |        |
| Brief Physical Exam                                                             |                                                          | x                                    |                                                                          |     |     |     |     |     |     |     |     |      |                                  |      |      |      |      |      |      |      |      |      |      | x                       | x    |        |
| Serum beta hcg (women < 2 years postmenopausal only)                | x                                                        | x                                    |                                                                          |     |     |     |     |     |     |     |     |      |                                  |      |      |      |      |      |      |      |      |      |      | x                       |      |        |

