#### Hematology

|                                                    |                     |                                    |
|----------------------------------------------------|---------------------|------------------------------------|
| Platelet Count                                     | RBC Indices: | Automated WBC Differential: |
| RBC Count                                          | MCV                 | Neutrophils                        |
| WBC Count (absolute)                               | MCH                 | Lymphocytes                        |
| Reticulocyte Count                                 | MCHC                | Monocytes                          |
| Hemoglobin                                         |                     | Eosinophils                        |
| Hematocrit                                         |                     | Basophils                          |
| PT-INR & aPTT for screen and 7 days follow-up only |                     |                                    |

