**Additional Follow-Up Procedures for subjects who meet *any* of the stopping criteria:**

- Viral hepatitis serology including:

- Hepatitis A IgM antibody;
- Hepatitis B surface antigen and Hepatitis B Core Antibody (IgM);
- Hepatitis C RNA;
- Cytomegalovirus IgM antibody;
- Epstein-Barr viral capsid antigen IgM antibody (or if unavailable, obtain heterophile antibody or monospot testing);
- Hepatitis E IgM antibody (if subject resides outside the USA or Canada, or has traveled outside USA or Canada in past 3 months)
- Blood sample for pharmacokinetic (PK) analysis, obtained within 2 months of last dose. Record the date/time of the PK blood sample draw and the date/time of the last dose of investigational product prior to blood sample draw on the CRF. If the date or time of the last dose is unclear, provide the subject's best approximation. If the date/time of the last dose can not be approximated OR a PK sample can not be collected in the time period indicated above, **do not obtain a PK sample**. Instructions for sample handling and shipping are included in the SPM.
- Serum creatine phosphokinase (CPK) and lactate dehydrogenase (LDH).
- Fractionate bilirubin, if total bilirubin  $\geq 2 \times \text{ULN}$ .
- Assess eosinophilia
- Record the appearance or worsening of clinical symptoms of hepatitis (fatigue, nausea, vomiting, right upper quadrant pain or tenderness, fever, rash or eosinophilia) as relevant on the AE CRF
- Record use of concomitant medications, acetaminophen, herbal remedies, other over the counter medications, or putative hepatotoxins on the Concomitant Medications CRF.
- Record alcohol use on the Liver Events CRF.

The following are required for subjects with ALT  $\geq 3 \times \text{ULN}$  **and** bilirubin  $\geq 2 \times \text{ULN}$  but are optional for other abnormal liver chemistries:

- Anti-nuclear antibody, anti-smooth muscle antibody, and Type 1 anti-liver kidney microsomal antibodies.
- Liver imaging (ultrasound, magnetic resonance, or computerized tomography) to evaluate liver disease.
- The Liver Imaging and/or Liver Biopsy CRFs are also to be completed if these tests are performed.

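### The SAE definition counts ALT ≥3×ULN with INR >1.5 as serious liver injury, but no liver monitoring rule uses INR, so this form of the SAE gets weekly checks and no prescribed repeat INR

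*Protocol*

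**What the plan says.** **SAE definition (Section 12.2, item g).** ALT ≥3×ULN with either total bilirubin ≥2×ULN or INR >1.5 is an SAE. The note adds that an INR above 1.5 points to severe liver injury, and then: "If INR is obtained, the value is to be recorded on the SAE form".

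**Section 4.5.4.** Every ALT ≥3×ULN means permanent withdrawal from the study, a report to GSK within 24 hours and a work-up. There are two intensities:
- With bilirubin ≥1.5×ULN, the rule reads ">35% direct bilirubin; bilirubin fractionation required) must be required to return to the clinic (within 24 hours) for repeat liver chemistries", followed by twice-weekly monitoring and a recommended specialist or hepatology consultation.
- ALT ≥3×ULN alone "must be monitored weekly until liver chemistries (ALT, AST, alkaline phosphatase, bilirubin) resolve, stabilize or return to within baseline values".

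**Section 4.5.5.1.** Five stopping criteria are built on ALT, bilirubin, symptoms or rash, persistence and the feasibility of weekly monitoring. They are tied to the first follow-up, 7 days after dosing.

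**Section 13.**
- ALT ≥3×ULN with bilirubin ≥2×ULN (Stopping Criterion #1) is labelled an SAE and calls for a return within 24 hours, a recommended consultation, and "Monitor subjects twice weekly until liver chemistries (ALT, AST, alkaline phosphatase, bilirubin) resolve, stabilize or return to within baseline values".
- Criteria #2 to #5 call for a return within 24–72 hours, then weekly checks.
- The lowest group (ALT ≥3 to <5×ULN, bilirubin <2×ULN, no symptoms or rash) calls for notice to the medical monitor within 24 hours, and "Liver chemistries (ALT, AST, alkaline phosphatase, bilirubin) can be monitored weekly for up to 4 weeks".
- Autoimmune antibodies and liver imaging are required with bilirubin ≥2×ULN "but are optional for other abnormal liver chemistries". Section 4.5.4 has the same split at bilirubin ≥1.5×ULN.

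**Schedule.** In Section 4.6 the row "Hema/Chem/Urinalysis tests" is marked at both follow-up visits, which footnote 7 sets at day 7 and day 56. In Section 7.2.5 the coagulation line reads "PT-INR & aPTT for screen and 7 days follow-up only".

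**The concern.** Section 12.2(g) treats bilirubin and INR as alternative signs of the same serious event. The sections that tell the site what to do carry only the bilirubin sign. A site following 4.5.4, 4.5.5.1 and Section 13 as written would give the INR form less intensive follow-up than the bilirubin form. After day 7, nothing in the schedule or the recheck panel would prompt the measurement that decides whether the event is an SAE at all.

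Two things are at stake: how closely a subject with suspected severe liver injury is watched, and whether that SAE is reliably found.

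**Working it through.** The plan gives no figure to reproduce. The check sets the rules side by side and then counts prescribed contacts and tests.

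**Step 1: is INR used anywhere in the liver rules?**
- Triggers: 4.5.4, 4.5.5.1 and Section 13 use ALT, bilirubin, symptoms or rash, and persistence. None uses INR.
- Recheck panel: ALT, AST, alkaline phosphatase and bilirubin in both 4.5.4 and Section 13. No INR.
- Work-up lists: viral serology, PK sample, CPK, LDH and bilirubin fractionation in both sections. No INR.
- The only INR criterion elsewhere is 4.5.5.3, at INR >2. It is not tied to ALT, sets no monitoring, and leaves INR >1.5 to 2.0 untouched.

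**Step 2: trace a case.** Take ALT 4×ULN, INR 1.8, bilirubin 1.2×ULN, no symptoms or rash.
- 12.2(g): SAE.
- 4.5.4: ALT-only tier, weekly.
- 4.5.5.1: no criterion met at onset; weekly.
- Section 13: lowest group, weekly for up to 4 weeks.

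**Step 3: vary ALT and symptoms.** With ALT ≥5×ULN, or with symptoms or rash, and the same INR and bilirubin, the subject moves to Criteria #2–#5 in Section 13. That adds a return within 24–72 hours. Monitoring stays weekly, and antibodies and imaging stay optional. So the boundary is set by bilirubin and not by ALT or symptoms: every INR-defined case that misses the 4.5.4 bilirubin trigger is monitored weekly. (If bilirubin is ≥2×ULN with a low direct fraction, Criterion #1 applies on bilirubin alone and the case is outside this point.)

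**Step 4: count contacts over an illustrative four weeks without resolution.**

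| Form of the SAE | Contacts |
|---|---|
| INR form, ALT ≥3 to <5×ULN, no symptoms | 4 weekly = 4 |
| INR form, ALT ≥5×ULN or symptoms/rash | 1 return + 4 weekly = 5 |
| Bilirubin form | 1 return + 2 × 4 = 9 |

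The differences are 9 − 4 = 5 and 9 − 5 = 4. If the early return counts as one of the scheduled checks, the bilirubin form has 8 contacts and both INR forms have 4, a difference of 4.

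**Step 5: count prescribed INR readings.** For detection plus four weekly rechecks (1 + 4 = 5 occasions), INR is prescribed at 1 of 5 if the ALT rise is found at day 7, and at 0 of 5 if it is found at day 56.

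These are counts of prescribed visits and tests in constructed cases. They are not estimates of affected subjects.

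**The case against.** The strongest reply is that 12.2(g) classifies events for reporting while the liver tiers set laboratory follow-up, and nothing says the two must match. Section 13 itself treats SAE status as a separate question, and 12.2(g) makes INR conditional on its having been obtained. This has some force. But Section 13 labels its Criterion #1 group an SAE by reference to 12.2 and gives that group the highest intensity. Having linked the two, it carries over one half of the definition and leaves out the other, which 12.2(g) itself describes as a sign of severe injury.

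Four further points stand and limit the concern:
- A reader might infer that such a subject gets weekly checks and nothing else. The text does not support that. Every ALT ≥3×ULN already brings withdrawal, a 24-hour report to GSK, notice to the medical monitor, viral serology, a PK sample and CPK/LDH. Sections 12.6 and 12.7 add SAE reporting within 24 hours, follow-up to resolution, and supplemental tests as indicated or requested. Those general duties set no frequency, however, and name no INR.
- A reader might infer that INR is missing when the stopping criteria are applied. It is not. 4.5.5.1 ties them to day 7, when PT-INR is drawn. The gap is at day 56 and at rechecks. A first ALT rise at day 56 would come about five half-lives after a single dose, on the protocol's own equation of 2 months with five terminal half-lives.
- Sections 7 and 7.2 allow extra safety time points. This permits an INR but does not prompt one.
- The contact counts depend on a four-week window without resolution and on how the early return is counted.

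**Conclusion.** As written, the safety rules are internally inconsistent: an event that 12.2(g) defines as serious is followed by rules that implement only one of its two limbs. The affected subjects are those with ALT ≥3×ULN, INR >1.5 and bilirubin below the 4.5.4 trigger, at any ALT level and with or without symptoms.

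The size is small. The difference is 4 to 5 prescribed contacts over four weeks, the consultation, and the required antibodies and imaging, plus an INR that is not prescribed after day 7. The protocol gives no event rate. With 20 to 35 subjects enrolled, and with coagulation disorders, anticoagulants and liver disease excluded, probably very few subjects would be affected.

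It might be inferred that dosing, cohort re-entry or the primary analysis is compromised. The documents do not support that. Each cohort is single dose, 4.5.4 and 10.3.2 already bar re-entry, and the primary endpoints are CSF amyloid levels on the dosing day. The effect is confined to follow-up intensity and SAE ascertainment. This is a correction that could be made at the next amendment and is not essential to the trial's conclusions.

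**What to change.** 1. Add INR >1.5 as an alternative to the bilirubin condition in the higher-intensity tier of 4.5.4 and its required-test list, in Stopping Criterion #1 of 4.5.5.1, and in the matching Section 13 group and its required tests. All three sections must change together; otherwise 4.5.4 would still say weekly where Section 13 says twice weekly. Limit the weekly-only descriptions in 4.5.5.1 and Section 13 to INR ≤1.5.
2. Require INR at detection and at each recheck whenever ALT is ≥3×ULN, using draws already made.
3. Leave the definition in 12.2(g) unchanged. Exclusion 23 admits subjects with INR up to 2, so some could enter above 1.5. If an allowance for baseline is wanted, apply it only to the monitoring tier and not to SAE reporting.

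**Cost.** Protocol wording, plus a few INR tests. With weekly checks this is at most 5 over four weeks per subject with ALT ≥3×ULN (4 if found at day 7, since one is already scheduled), and one more where the 24–72 hour return applies. A subject moved to the higher tier would have 4 to 5 more contacts, up to 1 + 9 = 10 INR readings, one antibody panel and one liver imaging. The downside is that a rare subject is followed more intensively than turns out to be needed.
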